At the recommendation of reviewers, we have deferred this resubmission until our pilot project was completed; the findings are not significantly different from what we previously described. The overall prevalence of transmitted HIV-1 drug resistance is somewhat lower (34% versus 46%) because subjects were studied in reverse chronologic order, and those recently studied were among those enrolled prior to 2000. However, we remain confident that the primary objectives of each of the aims will be sufficiently powered with continued enrollment of subjects with acute HIV-1 infection and their putative source partners during a planned five-year study period, as described in detail in **5. Research Design and Methods.**

Other concerns of reviewers are addressed below. Changes to the submission are indicated by italicized text.

Critique #1:

1. "…the proposed research … would not likely affect treatment options of HIV infected individuals." and "Most importantly, is this study relevant to clinical significance as patients can be diagnosed to be in virological failure and function normally with the diagnosis of acute HIV infection."

As mentioned above, results from these studies could modify current treatment practices. We agree with Reviewer #1 that low-frequency mutations may not, in fact, uniformly reduce the efficacy of ARV therapy, and there may be negative consequences if clinicians unnecessarily avoid effective ARV agents in favor of more complicated regimens. It also should be determined, even if low-level mutations are clinically relevant, if use of more-sensitive HIV-1 drug resistance assays prior to initiation of ARVs would be cost-effective.

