*Eighty-three (88%) of the 94 subjects initiated ARV therapy a median of 45 (IQR 24-107) days after HIV-1 infection. Four (5%) subjects who initiated ARV therapy had HIV-1 drug resistance mutations identified by consensus sequencing, 24 (29%) subjects had low-frequency mutations identified only by OLA, and 55 (66%) subjects had no mutations that were detected by either assay. At the start of ARV therapy, the mean CD4+ T-cell count was 451 (SD 197) cells/mm3 in subjects with low-frequency mutations and 479 (SD 168) cells/mm3 in subjects with no detectable mutations (p=.5). The mean HIV-1 RNA level at the start of treatment was 5.0 (SD 0.8) log10 copies/mL in subjects with low-frequency mutations and 4.8 (SD 1.0)* *log10 copies/mL in subjects with no detectable mutations (p=.4).*

*Survival analyses evaluated the time to virologic suppression (HIV-1 RNA less than 50 copies/mL) among treated PIC subjects. The HIV-1 drug resistance mutations that were detected in either plasma or PBMCs from each subject were evaluated with the Stanford University HIV Drug Resistance Database [151] in order to estimate the number of active agents in a subject's treatment regimen. An ARV agent was considered to be inactive if the mutation conferred high or intermediate-level resistance to that ARV. Cox proportional hazard models compared subjects with low-frequency HIV-1 drug resistance mutations receiving fewer than three active ARV agents ("inadequate" regimens) to subjects with low-frequency HIV-1 drug resistance mutations receiving at least three active ARV agents and to subjects without detectable mutations. Analyses were adjusted for HIV-1 RNA level at the time of initiation of ARV therapy.* ***Figure 4*** *shows the Kaplan-Meier curve indicating time to virologic suppression. After adjustment for the HIV-1 RNA level at the start of ARV therapy, the hazard ratio for time to virologic suppression was 1.1 (95% CI 0.54-2.3, p=.8) for 14 subjects with low-frequency HIV-1 drug resistance mutations who received fewer than three active ARV agents and 2.3 (95% CI 1.1-4.6, p=.02) for ten subjects with low-frequency mutations treated with at least three active agents, compared to 55 subjects without detectable mutations. (Note: a hazard ratio less than 1 indicates a longer time to virologic suppression, and a ratio greater than 1 indicates a shorter time to virologic suppression.).*

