**5. Research Design and Methods**

**5.a Overview of study design and rationale**

The studies proposed in this section will provide a better understanding of the prevalence and dynamics of low-frequency HIV-1 drug resistance mutations in ARV-naïve subjects during primary HIV-1 infection (**Aim #1**), the impact of low-frequency drug resistance mutations on response to ARV therapy (**Aim #2**), and the relative "transmission fitness" of mutant viruses (**Aim #3**). The project will be powered to perform the longitudinal analyses described in the first two studies with use of samples from *approximately 100* subjects who previously enrolled in the PIC Cohort study within 30 days after HIV-1 infection and from *80* subjects who will be enrolled prospectively. Eligibility will be restricted to subjects who acquired HIV-1 infection after 1996, when highly active ARV therapy became widely available in Seattle. OLA will be used to evaluate HIV-1 drug resistance in the PBMCs, blood and seminal plasma from ARV-naïve PIC subjects at baseline (the first available specimen), and 6 and 12 months after HIV infection (**Aim #1)** and in PBMCs 6 and 12 months after the start of ARV therapy (**Aim #2)** to detect changes in the levels of low-frequency HIV-1 drug resistance over time.

The third aim will study PIC subjects and their source partners enrolled in the PIC Cohort and PIC Partners studies. After the transmission relationships are confirmed by molecular methods, this cross-sectional analysis will compare the results of HIV-1 drug resistance testing performed on PBMCs and blood plasma from PIC subjects with the results of resistance testing performed on PBMCs, blood plasma, and genital secretions from their confirmed source partners. The partner-pairs studied in this third aim will also include retrospective analysis of previously collected specimens and continued prospective enrollment in order to maximize the precision of estimates of "transmission fitness" to be described in **5.c.3 Aim #3**.

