**Table 10: Precision estimates for proportions of subjects with new drug resistance mutations detected**

| Sample size | 10 | 20 | 30 | 40 | 50 | 100 |
| --- | --- | --- | --- | --- | --- | --- |
| 95% confidence interval (+/-) | .31 | .23 | .19 | .16 | .14 | .10 |

With the increased study size compared to the pilot project, we will perform a definitive analysis to assess the impact of low-frequency mutations on time to virologic suppression (defined as HIV-1 RNA less than 50 copies/mL). Survival analyses will evaluate the time to virologic suppression among subjects with transmitted low-frequency HIV-1 drug resistance mutations detected who are on ARV regimens with fewer than three active agents compared to subjects without transmitted HIV-1 drug resistance, controlling for the baseline HIV-1 RNA level. If a significant difference is detected, we will use additional Cox proportional hazard models to explore characteristics (e.g. HLA type, specific mutation or class of ARV therapy, and timing of ARV treatment) that might impact time to virologic suppression.

We will also perform a survival analysis evaluating the time to virologic failure among subjects with transmitted low-frequency HIV-1 drug resistance mutations who are on ARV regimens with fewer than three active ARV agents compared to subjects without transmitted HIV-1 drug resistance, controlling for baseline HIV-1 RNA level and the timing of initiation of ARV therapy. For purposes of this analysis, virologic failure will be defined as any one of the following:

1) Failure to suppress viral replication (HIV-1 RNA greater than 400 copies/mL after 24 weeks or greater than 50 copies/mL on two occasions after 48 weeks)

2) Addition or substitution of ARVs because of delay in viral suppression

3) Detectable HIV-1 RNA (greater than 400 copies/mL) on two consecutive occasions following viral suppression

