**5.e.2 HIV-1 RNA quantification in blood plasma and genital secretions**

Blood plasma HIV-1 RNA quantification is performed by an independently-validated real-time RT-PCR amplification assay with lower limits of detection equal to 50 copies/mL [195]. Results of specimens collected between 1996 and 2002 were initially tested with branched DNA (bDNA) assays with lower limits of detection of 50 and 500 copies/mL (Chiron Corporation, Emeryville, CA). When specimens were available, results censored at 500 copies/mL have been re-tested using an ultra-sensitive reverse transcription polymerase chain reaction (RT-PCR) assay (Roche, Branchburg, NJ) or the real-time RT-PCR assay. Since 2002, all specimens have been evaluated by an RT-PCR assay.

Semen is processed within two hours of collection [196]. Specimens are diluted to reduce viscosity and centrifuged to separate the seminal plasma and cell pellet. Boom (silica) extraction is performed to minimize effect of inhibitory factors, and HIV-1 RNA is quantified using the real-time RT-PCR assay (lower limit of detection equal to 300 copies/mL) or Roche Amplicor HIV-1-1 Monitor versions 1.0 or 1.5 (lower limit of detection equal to 200 copies/mL) [197]. For both blood and semen, specimens with HIV-1 RNA levels below the lower limits of detection will be assigned censored values.

For women, CVL fluid is transported on ice and centrifuged after arrival at the laboratory, and the supernatant is frozen at –80oC. The cytobrush is put into PBS and agitated, the cells are separated by centrifugation, and the cell pellet is stored at –80oC. These specimens will be used for RNA quantitation and OLA.

**5.e.3** RT-PCR and PCR for genotyping of HIV-1 *pol*

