**5.g Timetable for all projects**

Y1 0-6 months Submission of modification to IRB application

Confirmation of yet-to-be confirmed transmission pairs in PIC Partner Study

Continued enrollment in PIC Cohort and PIC Partners Studies (through Y5)

Y1-2 OLA of source and recipient partner-pairs (Aim #3)

Y2-3 OLA of untreated subjects (Aim #1)

Data analysis and manuscript preparation of Aim #3

Y3-4 OLA of treated subjects (Aim #2)

Data analysis and manuscript preparation of Aim #1

Y4-Y5 Data analysis, manuscript preparation of Aim #2 and future grant submission

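### The Aim 2 time-to-suppression model omits calendar period, although the protocol ties era to both baseline resistance and RNA measurement; the effect estimate may be confounded in either direction

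*Protocol*

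**What the plan says.** Section 5.a sets the calendar span: "Eligibility will be restricted to subjects who acquired HIV-1 infection after 1996, when highly active ARV therapy became widely available in Seattle". Stored specimens are combined with prospective subjects, and the timetable in 5.g plans "Continued enrollment in PIC Cohort and PIC Partners Studies (through Y5").

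For primary objective 2 of Aim 2, section 5.c.2 (text after Table 10) describes a survival analysis, which it calls definitive, of time to RNA below 50 copies/mL. The covariate set and the next step are stated together: "controlling for the baseline HIV-1 RNA level. If a significant difference is detected, we will use additional Cox proportional hazard models to explore characteristics". The listed characteristics are HLA type, mutation or ARV class, and timing of ARV treatment. Calendar year is not among them. The companion analysis of virologic failure adds only timing of ARV initiation.

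Two other sections bear on era:

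- Section 1, on exposure: "The overall prevalence of transmitted HIV-1 drug resistance is somewhat lower (34% versus 46%) because subjects were studied in reverse chronologic order". The same sentence explains that the subjects tested last had joined the cohort before 2000.
- Section 5.e.2, on measurement: specimens from 1996 to 2002 were "initially tested with branched DNA (bDNA) assays with lower limits of detection of 50 and 500 copies/mL". Results censored at 500 were retested only when specimens were available. RT-PCR has been used for all specimens since 2002.

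**The concern.** A confounder has to be related to both the exposure and the recorded outcome. The protocol supplies a link on each side. By its own account, earlier enrollees carry less detected resistance, so the comparator without resistance is weighted toward the early years. In those years some RNA results could not be classified against the 50-copy threshold at all, because a result below 500 may lie on either side of 50.

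The only stated adjustment is baseline RNA, which does not carry this information. ARV class might act as a partial proxy for era, but it is examined only after a significant first result. If era pulled the estimate toward the null, that step would never be reached. The result bears on whether more-sensitive resistance testing should be pursued (section 2, Aim #2 implications), so an era artefact in either direction could mislead.

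**Working it through.** **1. The plan's own figures.**
- Pilot prevalence (4.g): (6 + 28)/100 = 34%, as stated.
- Pilot hazard ratios, p-values rebuilt from the intervals with SE = (ln upper − ln lower)/3.92. For 1.1 (0.54-2.3): SE 0.370, p = 0.80. For 2.3 (1.1-4.6): SE 0.365, p = 0.022. Both match the stated .8 and .02.
- The protocol gives no power figure for time to suppression, so there is none to reproduce.

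**2. How strongly era is tied to resistance.** The number tested when prevalence stood at 46% is not given. If it was m of the final 100, prevalence in the later-tested, earlier-enrolled remainder is (34 − 0.46m)/(100 − m):

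| m (assumed) | Prevalence in remainder |
|---|---|
| 40 | 26% |
| 50 | 22% |
| 60 | 16% |
| 70 | 6% |

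**3. What this could do to the estimate.** This is an illustration by simulation, and every input below is an assumption. Half the subjects come from each era; the true hazard ratio for resistance is 0.60; times are exponential with a 12-week baseline median; log10 RNA has mean 4.9 and SD 0.9, with log-hazard −0.3 per unit; visits fall at weeks 1, 2, 3, 4, 8, 12, 16, 24, 48 and 72. In the last two columns there is no true era effect, but half of early-era subjects have suppression dated 8 weeks late (an unretested result below 500 not counted as suppressed) or 8 weeks early (counted as suppressed). Entries are the hazard ratio from the Cox model adjusted for RNA only:

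| Resistance early / late | Late-era HR 0.67 | Late-era HR 1.5 | Late-era HR 2.0 | Dated late | Dated early |
|---|---|---|---|---|---|
| 22% / 46% | 0.55 | 0.71 | 0.75 | 0.65 | 0.59 |
| 16% / 46% | 0.53 | 0.70 | 0.76 | 0.65 | 0.58 |
| 6% / 46% | 0.51 | 0.74 | 0.88 | 0.68 | 0.57 |
| 34% / 34% | 0.62 | 0.61 | 0.62 | 0.61 | 0.59 |

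Stratifying the same model by era gives 0.59 to 0.63 in all these cells. Without a link between era and resistance (last row) there is no material bias.

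**4. Whether the follow-up models would be reached.** Power = Φ(|ln HR| × √(d·p·(1 − p)) − 1.96). Take p = 14/69 = 0.20, from the pilot's 14 subjects on fewer than three active agents and 55 without mutations, and assume d = 100 events. The square root is 4.02.

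| HR as estimated | Power |
|---|---|
| 0.60 | 54% |
| 0.71 | 28% |
| 0.75 | 21% |
| 0.88 | 7% |

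A moderate shift toward the null therefore makes it considerably less likely that the exploratory models are fitted at all.

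**The case against.** Several points on the other side stand.

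- **Direction.** A reader might infer that era must hide harm. The documents do not support that. They give no era-specific response and no rule for classifying unretested results below 500, beyond saying in 5.e.2 that values below the limit are assigned censored values. The table shows the bias reversing.
- **Size.** Both m and the era effect are assumed. At m = 40 the split is about 18/40 versus 16/60 (Fisher p = 0.08), which is a modest link. Resistance is tied to enrollment before 2000 and the assay change to 2002; the illustration merges the two, which overstates their overlap.
- **Population.** The 53 treated subjects planned for the new-mutation comparison are 20 from the pilot, 20 enrolled since it began, and about 42 × 0.33 × 0.9 = 12.5 prospective. Pilot subjects are then at most 20/53 = 38%, and not all are early-era. With a 20% early share and 22% early resistance, a true hazard ratio of 1.0 reads only about 1.1 when late-era suppression is 1.5 to 2.0 times faster. How many further pilot subjects enter the suppression analysis is not stated.
- **Pilot result.** It is tempting to read "2.3 (95% CI 1.1-4.6, p=.02) for ten subjects with low-frequency mutations treated with at least three active agents" as a sign of confounding. It rests on ten subjects outside the planned contrast. The group inside that contrast had 1.1 (0.54-2.3). Neither figure identifies era as a cause.

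One could also say that covariates belong in an analysis plan. But 5.c.2 states its covariate set and makes anything further depend on significance. Section 5.c.1 names year of HIV-1 acquisition for Aim 1, and 4.d splits controls into historical and contemporary groups because of baseline differences. Section 5.h.3 concedes confounding in general terms; the limitations in 5.f do not mention era.

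**Conclusion.** The concern holds as possible confounding by calendar era of undetermined direction and size. What rests on the text is the pooling of infections from after 1996 through year 5, the protocol's own link between era and resistance prevalence, the era-dependent assay limit with incomplete retesting, and a stated model containing baseline RNA alone. What rests on assumption is every shifted hazard ratio above: a true 0.60 reading 0.65 to 0.88 in one direction or 0.51 to 0.59 in the other. Retesting reduces the assay part to an unstated degree. The gate on significance makes the plan weaker against masking than against exaggeration, but that asymmetry is not evidence that masking occurs. The Table 9 sample size is unaffected. The correction is worth making because it is cheap and the confounder is one that the protocol itself identifies.

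**What to change.** In 5.c.2, add calendar period of ARV start to the primary Cox model for time to suppression, as one prespecified term or stratum (for example before versus from 2002, the assay change), and do not make it conditional on a significant first result. State how results below 500 copies/mL that were not retested are handled: treat them as interval-censored for the 50-copy endpoint, or add a sensitivity analysis limited to results from assays with a 50-copy limit.

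Nothing more is needed here. Mandatory adjustment for regimen class would condition on part of an exposure that is defined by the number of active agents. A second calendar cut would thin the data, with only about 18 resistant subjects in the planned Aim 2 sample. The new-mutation comparison uses OLA in PBMCs rather than the RNA assay, and this point does not require stratifying it.

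The cost is one extra model term and somewhat wider intervals. Section 4.b says HIV-1 RNA records are available at regular intervals, so no new data collection should be required.

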**5.c.3 Aim #3: Compare HIV-1 drug resistance patterns in PIC subjects and their source partners.**

This cross-sectional study will evaluate the prevalence and patterns of HIV-1 drug resistance in partner-pairs and compare results of HIV-1 drug resistance testing in the PBMCs, blood plasma, and genital secretions (when available) from the confirmed source partner with test results in PBMCs and blood plasma from the recipient partner. We hypothesize that HIV-1 drug resistant variants will have lower "transmission fitness" compared to wild-type variants, and drug resistance will occur less frequently and at lower levels in the PBMCs and plasma from PIC subjects than in the PBMCs, blood plasma, and genital secretions from their confirmed source partners. Because the most common risk for HIV-1 acquisition reported among our cohort is receptive anal intercourse, the ideal comparison would evaluate the results of HIV-1 drug resistance testing in semen specimens from every source partner. However, not all potential source partners collect genital secretions for study. As previous studies have shown that there is moderate concordance between HIV-1 drug resistance testing results in blood and semen [61-63], our proposed comparison using the results of resistance testing in the blood of source partners should have relevance.

For every subject enrolled in the PIC Cohort study, we will attempt to identify and study all source partners through the methods described below in **5.d.2 PIC Partners study** and **5.e Laboratory methods**.If OLA is not performed as part of the other studies previously described in this application, OLA will be performed on the first available PBMC and plasma specimens from PIC enrollees and on the PBMC, blood plasma, and genital secretions from confirmed source partners. We hypothesize that many but not all mutations in the source partner will be identified in the recipient partner and that low-frequency mutations detected in the recipient partner will be present at lower levels compared to their levels in the source partners. Secondary analyses will explore whether the probability of transmission differs between specific HIV-1 drug resistance mutations.

Analysis for the primary objective will be calculated as a binomial probability of the number of mutations transmitted from each source partner to the recipient partner, conditional on the number of mutations in the source partner. This accounts for the fact that source partners will undoubtedly have different numbers of HIV-1 drug resistance mutations. For the purpose of sample size calculations, we assume that the number of mutations in the source partners follows a Poisson distribution with the expected number of mutations being two. Power calculations are based on simulations, repeated 1000 times. Each simulation estimates the binomial probability of transmitting a mutation conditional on the number of mutations in the source partners, and calculates the associated 95% confidence intervals based on normal approximation for the estimated probability. The type II error is calculated as the number of simulation replicates where the 95% confidence interval contains the value of 1, when the simulated transmission probability is less than 1.

Using the simulation analyses described above, we will have 82% power to detect a transmission probability of all source partner mutations of 80% or less if we have 17 confirmed partner-pairs in which the source partner has at least one HIV-1 drug resistance mutation. *Overall, the subset of recipient partners who had resistance identified by OLA (4/12=33%) was similar to the population studied in the pilot project. Of the 18 confirmed partner pairs without complete OLA testing, we would expect 6 to 18 source partners to have HIV-1 drug resistance. Based on our prior experience with confirming putative source partners, we would expect that the relationship of 14 of the remaining 17 partner-pairs would be confirmed, and 5 to 17 of these source partners would have HIV-1 drug resistance. We would therefore need to enroll at most 21 (and likely fewer) new putative source partners in order to have at least 6 additional confirmed source partners with HIV-1 drug resistance.*

To further explore which specific mutations are more likely to be transmitted and result in subsequent HIV-1 infection, we will conduct a logistic regression analysis with generalized estimating equations to account for correlation of the presence of different mutations within the same source partner. In this analysis, each individual mutation will be evaluated, with the outcome in the regression model; transmitted to partner Yes/No. Indicator covariates will be used to identify specific mutations. To account for the potential loss of detection of mutants over time, an exploratory analysis will adjust for the estimated time between the transmission event and the dates samples are obtained from the transmission pair for HIV-1 drug resistance testing.

We will also use the semi-quantitative nature of OLA to categorize HIV-1 drug resistance mutations as comprising <5%, 5-10%, 10-30%, 30-50%, and 50-100% of the viral quasi-species. We will compare the level of specific HIV-1 drug resistance mutations in the source and recipient partners to identify, for example, whether a mutation exists as 5-10% of the population in the source partner but 10-50% in the recipient. Analyses will control for HIV-1 RNA levels at the time of HIV-1 transmission.

